### Informed Consent and Participant Privacy

Our consent and privacy processes closely follow the consent protocols established by Karra and Canning [40]. The process of obtaining consent was consistent for all potential participants: women and eligible husbands. Written consent to participate was obtained from all the participants before administering the surveys. Once participants agreed to join the study, a copy of the consent form script was read to them, and they were given opportunities to ask questions and express concerns. Surveyors checked for comprehension throughout the consent process, which took 5-10 minutes on average. Multimedia Appendix 1 presents the consent documents and details of the consent process. After completing the consent script, potential participants were asked if they would like to participate. If the participant wished to take further time to reflect, then the surveyor and the participant would determine the time and method of reconnecting. If the potential participant agreed to participate in the study, then consent was obtained and documented by obtaining the signatures of both the participant and the study staff member who provided consent. Upon providing consent, the surveyor would then conduct the survey.

For follow-up surveys, written consent to participate was obtained from women who were followed up either at home or at the clinic, and verbal consent to participate was obtained over the phone from participants who were originally recruited at baseline but who did not visit the clinic over the intervention period. Respondents who had previously indicated that they were no longer interested in participating in the study were not contacted. All survey responses were collected on Android (Google LLC)-based tablets, and data were securely transferred to the CommCare-supported server daily.

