We will conduct several subgroup analyses to examine how our family planning intervention effects vary across key subpopulations. Subgroups of interest include women who have or do not have their husbands’ approval for accessing contraceptive methods, women who have or have not previously used family planning methods, women whose most valued method attribute is or is not effective, working or nonworking women, higher or lower educated women, counseling sessions administered in the morning or afternoon, women who have more or less than 2 children, and counseling sessions of above or below the median length.

Finally, robustness checks (5% and 10% sample truncations and coarsening of independent variables) and falsification tests, which include placebo regression, simulation, and resampling methods, will be conducted to ascertain the strength and significance of our estimates. We will also conduct attrition-adjusted analyses to assess the extent of differential loss-to-follow-up on outcomes. In handling missing data, we will conduct a complete case analysis if the potential impact of the missing data is negligible, and we can conduct a series of sensitivity analyses, including *best-worst* case analyses, to generate plausible bounds of estimates across different scenarios of missingness. If we are able to assume that any missing data are missing at random, then we will conduct an ITT analysis using multiple imputation to adjust for missing data. We will then compare the ITT estimates from our multiple imputation analysis with our estimates from a complete case analysis, which would allow us to infer the extent to which missingness might impact our inference.

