## Results

### Recruitment, Study Sample, and Randomization

Field activities for the baseline survey began with field staff hires, training, and piloting of the survey instrument in June 2019 and continued through September 2019. During the 3-month baseline survey period, 1122 women were approached and screened using the eligibility criteria. On the basis of the eligibility screening, of the 1122 women, 823 (73.4%) were found to be eligible to participate in the study. Of the 823 eligible women, 801 agreed to go through the consent form with the enumerator, and 785 (95.3% of the eligible sample) further consented to participate and were subsequently enrolled in the study. Of these 785 women, 782 (99.6%) completed the baseline survey and were eligible to be randomized into 1 of the 3 intervention groups or the control group. From this baseline sample, 223 women were randomly assigned to treatment (T1) with long counseling and husband invitations, 225 women were assigned to treatment (T2) with short counseling and no husband invitations, 228 women were assigned to treatment (T3) with short counseling and husband invitations, and 108 women were assigned to treatment (T0) with long counseling and no husband invitations. Among the 782 women in the final sample, 41 were interviewed as a part of a preliminary pilot study to test the feasibility of the survey instruments and implementation of the intervention. As part of the intervention rollout, these 41 respondents were also randomized into the T1 (n=10), T2 (n=13), T3 (n=12), and control T0 (n=6) arms. The final analytic sample for the baseline survey comprised 782 eligible women, of which 223 were assigned to T1, 225 were assigned to T2, 228 were assigned to T3, and 108 were assigned to T0 (control). The experimental framework is illustrated in Figure 1.

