### Follow-Up Surveys

Follow-up surveys began in November, 2 months after the conclusion of the baseline survey. Field activities for the follow-up surveys began with hiring field staff, training, and piloting the follow-up survey instruments in November 2019, which continued through February 2020. During the 4-month follow-up survey period from November 2019 to February 2020, 767 women (including 727 women from the main study and an additional 40 women from the pilot phase of the study, but not including the 15 women who withdrew from the study before the start of the follow-up survey) were reached. Of the 767 women who were reached at the follow-up stage, 731 (95% of women who were eligible for follow-up) successfully completed the follow-up survey. In total, 51 women who were interviewed at baseline are estimated to be lost to follow-up.

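### Comparing multiple imputation with complete case cannot show that losing 51 women is harmless; the best-worst bounds the plan already names should be mandatory and carry that judgement

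*Protocol article*

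**What the plan says.** The last paragraph of the protocol article's Analysis Plan sets out the handling of missing data in five parts:

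- Attrition-adjusted analyses *will* be done to look at differential loss.
- Complete case is used under a condition: "we will conduct a complete case analysis if the potential impact of the missing data is negligible". No criterion for negligible is given.
- Sensitivity analyses, including best-worst case analyses over several missingness scenarios, are something the authors *can* do.
- If missing at random can be assumed, an intent-to-treat analysis with multiple imputation *will* be done.
- The imputed and complete-case estimates are then compared, "which would allow us to infer the extent to which missingness might impact our inference".

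The extent of loss is known. Under Recruitment, Study Sample, and Randomization: "The final analytic sample for the baseline survey comprised 782 eligible women". Under Follow-Up Surveys: "731 (95% of women who were eligible for follow-up) successfully completed the follow-up survey", a count of those reached "not including the 15 women who withdrew from the study before the start of the follow-up survey", and "In total, 51 women who were interviewed at baseline are estimated to be lost to follow-up". Under Informed Consent and Participant Privacy: "Respondents who had previously indicated that they were no longer interested in participating in the study were not contacted".

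**The concern.** The closing sentence is an inference rule: the size of the gap between the two estimates tells the reader how much missingness matters. For one kind of missingness that is fair. If loss depends on recorded variables that the imputation uses and the complete-case analysis does not, the gap shows how much this matters. For the other kind it is not. If women who stopped using a method, or never took one up, are harder to survey, both estimates are biased in the same direction and the gap between them can be small.

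The sequence makes this worse. Imputation is run only after missing at random has been assumed, so the comparison is made only once the troublesome case has been set aside. The tool that does not need that assumption, the best-worst bounds, is the one worded as optional.

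The follow-up design gives a reason to take the question seriously. Women who visited the study clinic were surveyed there. The others had to be reached by up to three calls and then one home visit. Being surveyed is therefore linked to seeking care after counselling, which lies close to contraceptive uptake. This is a reason to check, not evidence that dropout was informative.

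At stake is whether the trial may describe its effect on contraceptive use as robust to attrition.

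**Working it through.** **1. Reproduce the loss.** From Follow-Up Surveys and the baseline sample: 782 − 731 = 51, and 51/782 = 6.5%. The parts agree: 782 − 767 = 15 withdrew and 767 − 731 = 36 were reached but did not complete; 15 + 36 = 51. (The four published arm sizes, 223 + 225 + 228 + 108, sum to 784, not 782. This makes no material difference here.)

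**2. Do the two methods share one assumption?** No. A simulation used 451 invited women (223 + 228) and 333 non-invited women (225 + 108), 400 replicates, and a baseline factor that is present in half the women and shifts use from 25% to 75%, plus 10 points if invited. Imputation was within arm by that factor. The loss probabilities are assumptions, chosen to give about 6.5% loss per group.

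| Loss depends on | Full-data difference | Complete case | Imputation |
|---|---|---|---|
| Baseline factor (2% or 11%, reversed between groups) | 0.102 | 0.127 | 0.103 |
| Outcome (invited: 2% of users, 13% of non-users; non-invited: 11% of users, 2% of non-users) | 0.097 | 0.150 | 0.137 |

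In the first row imputation removes the bias and the gap is informative. In the second row the gap is 0.150 − 0.137 = 1.3 points, while imputation is still wrong by 0.137 − 0.097 = 4.0 points.

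**3. Check the second row without simulation.** The true rates are 60% and 50%.
- Complete case, invited: 0.60×0.98 / (0.60×0.98 + 0.40×0.87) = 0.628. Non-invited: 0.50×0.89 / (0.50×0.89 + 0.50×0.98) = 0.476. Difference 0.152.
- Imputation applies the same formula within each level of the baseline factor and averages. Invited: (0.865 + 0.378)/2 = 0.621. Non-invited: (0.732 + 0.232)/2 = 0.482. Difference 0.139.

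Against a truth of 0.10, the biases are 5.2 and 3.9 points and the gap is 1.3 points. This agrees with the simulation.

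**4. What the bounds would show.** Take the plan's own rates, 60% v 50% (Tables 4 and 6), as the observed rates, with 6.5% loss in each group (an assumption; losses by arm are not given). Observed share = 731/782 = 0.9348; lost share = 0.0652.
- Lower: 0.60×0.9348 − (0.50×0.9348 + 0.0652) = +2.8 points.
- Upper: (0.60×0.9348 + 0.0652) − 0.50×0.9348 = +15.9 points.

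If all 51 losses fell in the invited group, the bounds would be about +3.2 to +14.5. If all fell in the non-invited group, they would be about +2.3 to +17.7. The rates and the planned 400 v 300 split are the same for targeted v standard counselling, so the equal-loss bounds apply there too.

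**5. Milder scenarios.** Assume true use of 60% in the invited group, random loss in the other group, and use of *q* among lost invited women. Complete-case bias = (0.60 − 0.0652*q*)/0.9348 − 0.60. For *q* = 45%, 30% and 0% this gives +1.0, +2.1 and +4.2 points. For scale, the standard error at 60% v 50% with about 418 v 313 women observed is √(0.24/418 + 0.25/313) = 3.7 points.

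**The case against.** A reader might infer four stronger things, and the document supports none of them.

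- *That complete case and imputation rest on the same assumption.* They do not. Complete case needs loss unrelated to the outcome given the covariates in the analysis model. Imputation needs only missing at random and may use further variables. The first row of the simulation shows the difference.
- *That informative dropout would go undetected.* The section names best-worst bounds, which do not need missing at random, and commits to attrition-adjusted analyses. The latter are described only as addressing differential loss, with no method that handles outcome-dependent loss, but they cannot be ignored.
- *That imputation can do little more than repeat complete case because only arm and baseline data exist.* Table 3 marks contraceptive use and preferences as collected at counselling, and the Postcounseling Survey section describes asking for the preferred method straight after it. Such data could narrow the bias, and imputation by baseline factor alone may understate what is recoverable.
- *That the husband-related passages show arm-specific informative dropout.* Those passages, in the sample size section, concern which husbands attend and what women disclose. They do not discuss loss. No reasons for the 51 losses and no split by arm are given.

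The other side can also say that the closing sentence is hedged, that it applies only under missing at random, and that the plan nowhere says agreement proves attrition harmless. Loss of 6.5% is modest, best-worst limits are extreme by construction, and the mildest scenario above is about 1.0/3.7 = 0.3 standard errors. Delta ranges and the imputation model are details that a condensed article may leave to a full plan, so their absence is no fault.

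All of that stands and keeps the point small. It does not rescue the inference rule. The sentence gives the comparison a job that it cannot do for outcome-dependent loss, and the check that can do it is optional.

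**Conclusion.** The point holds in a limited form. The gap between imputation under missing at random and complete case measures sensitivity to missingness explained by observed data. It says nothing reliable about dropout that depends on the unobserved outcome, so agreement cannot show that losing 51 of 782 women is harmless.

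The size is moderate. On a 10-point difference the plan's own bounds would run from about +2.8 to +15.9 points, assuming observed rates of 60% v 50% and equal loss. Less extreme, assumed scenarios give 1 to 4 points of bias. The document does not show that dropout was in fact informative, and none of these figures is an estimate of actual bias. This is a cheap improvement to what the trial may claim about robustness, not a flaw in the main analysis.

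**What to change.** In the missing-data paragraph of the Analysis Plan:

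1. Limit the closing sentence to say that the comparison shows sensitivity to missingness explained by observed data only.
2. Change *can* to *will* for the best-worst bounds. Report them for the binary main outcomes on both factorial contrasts (invited v non-invited, targeted v standard).
3. Base any statement that missingness is negligible, or that the result is robust, on those bounds. Because they are extreme, an arm-specific delta-adjusted imputation may be added as a more realistic range; this is optional.
4. Include the counselling-wave data in the imputation model.

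The data are already collected, so the cost is wording and a few extra runs. The downside is that the robustness statement may be less favourable.

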### Sample Size and Power Calculations

#### Target Sample and Key Outcomes

The sample size of this study was powered to primarily identify the independent effects of tailored family counseling and male involvement on women’s contraceptive uptake and switching of methods. On the basis of the preliminary power calculations for the primary outcomes of interest, our target baseline sample consists of 700 eligible women who consent to participate in the study. Among these 700 women, 100 women were assigned to the control arm T0, and 200 women were assigned to each of the 3 intervention arms, namely, T1, T2, and T3.

Previous studies have found that one-fifth of women of reproductive age were either pregnant or had given birth to a child in the past 6 months [40]. To meet our target sample size of 700 women who would be eligible to participate in our study, we need to recruit a total of 940 women if we conservatively assumed a combined ineligibility or refusal rate of 25%.

We have powered our study to detect effects on the following outcomes: (1) contraceptive uptake and (2) intention to switch from the current contraceptive method.

#### Contraceptive Prevalence: Partner Invitation Interventions

Using modern contraceptive prevalence estimates for urban area of Malawi from the 2010 Malawi DHS, we assume a modern contraceptive prevalence rate of 50% among women aged 18-35 years who are currently not pregnant and who did not give birth in the 6 months before the baseline. To infer a potential effect size for our intervention, we look to evidence to a study from Zambia [28], which found that male involvement in family planning care-seeking decreased the probability of receiving family planning services by 19% over a 2-year study period. Our study differs from this study in that we do not require husbands to participate in the counseling session; instead, we leave it up to the woman to decide whether she would like to invite her husband to counseling or not. In designing our invitation in this way, a selection effect might exist, in which husbands who are more supportive of contraceptive use are more likely to comply with the intervention and participate in a joint counseling session. As a result, our male partner invitation intervention would likely lead to an increase in contraceptive prevalence.

Assuming an attrition-adjusted sample of 700 women, with 400 women assigned to partner invitation arms, T1 and T3, compared with 300 women assigned to noninvitation arms, T0 and T2, we will have 75% power to detect a percentage point increase of 10 in the contraceptive prevalence rate from 50% to 60% (α=.05, two-sided). If, instead, we use a one-sided test, then we estimate that we would have 85% power to detect the same 10 percentage point increase in contraceptive prevalence.

Table 4 presents the levels of power (1−β) that could be achieved for various minimum effect sizes for the modern contraceptive prevalence use, assuming a baseline contraceptive prevalence rate of 50% in both the intervention and control arms and a fixed endline sample size of 700 women.

**Table 4 table4:** Power calculations for contraceptive prevalence rate, partner invitation intervention.

Control CPR^a^, n (%)	Intervention CPR, n (%)	Significance level, α	Control sample size, n	Intervention sample size, n	Power
150 (50)	236 (59)	.05	300	400	0.66
150 (50)	240 (60)	.05	300	400	0.75
150 (50)	244 (61)	.05	300	400	0.83
150 (50)	248 (62)	.05	300	400	0.89

^a^CPR: contraceptive prevalence rate.

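### The baseline target and the supposedly attrition-adjusted endline sample are both 700, so the stated power allows for no loss to follow-up; the effect is small

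*Protocol article*

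**What the plan says.** Under Target Sample and Key Outcomes, 700 is an enrolment figure: "our target baseline sample consists of 700 eligible women who consent to participate in the study". The arms follow from it: "Among these 700 women, 100 women were assigned to the control arm T0, and 200 women were assigned to each of the 3 intervention arms". The Randomization section gives the same arm sizes. Recruitment and Study Timeline says recruitment ended once at least 700 eligible, consenting women had been given the baseline survey.

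The four power sections use 700 as a number left after loss. The first, on contraceptive prevalence and partner invitation, reads "Assuming an attrition-adjusted sample of 700 women, with 400 women assigned to partner invitation arms", "compared with 300 women assigned to noninvitation arms, T0 and T2". It introduces Table 4 as resting on "a fixed endline sample size of 700 women". The other three sections, with Tables 5 to 7, use the same wording and the same 300 v 400 split. For 50% v 60% the text says "we will have 75% power to detect a percentage point increase of 10" points, two-sided, and gives 85% for a one-sided test. For intention to switch, 20% v 30%, it gives 86% and 92%.

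The step from 940 to 700 is attributed to a 25% combined ineligibility or refusal rate. On actual loss, Follow-Up Surveys reports "51 women who were interviewed at baseline are estimated to be lost to follow-up", with 731 of 782 completing.

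**The concern.** One number is used both for women enrolled and for women remaining after attrition. The two agree only if nobody is lost. The 300 and 400 in Tables 4 to 7 are sums of the arm sizes as assigned (100 + 200 and 200 + 200), so nothing was taken off for loss.

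This goes beyond a detail that an article leaves to a fuller document. The article asserts that an adjustment was made, and its own figures show that it was not. A reader who takes the label at face value will think loss to follow-up is already in the 75% and 86%. That matters most for contraceptive prevalence, where two-sided power is modest even before any loss and a null result would have to be read against it.

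**Working it through.** **Inputs from the protocol article**
- Planned comparison: 300 v 400, α = 0.05.
- Rates: 50% v 60% (use) and 20% v 30% (switching).
- Stated power: 75% and 86% two-sided; 85% and 92% one-sided.
- Observed loss: 51/782 = 6.5%.
- Randomized arms as reported: T0 108, T1 223, T2 225, T3 228. These sum to 784 against a stated 782, a difference too small to matter here.

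**Formula.** Two-proportion normal approximation with pooled variance under the null and no continuity correction:

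power = Φ[(d − z·SE0)/SE1], where SE0 = √{p̄(1−p̄)(1/n1 + 1/n2)}, SE1 = √{p1(1−p1)/n1 + p2(1−p2)/n2}, p̄ is the size-weighted mean rate, and z = 1.960 (two-sided) or 1.645 (one-sided).

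**Step 1: reproduce the stated figures at 300 v 400**
- Use: p̄ = (150 + 240)/700 = 0.557, SE0 = 0.0379, SE1 = 0.0379. Two-sided Φ(0.677) = 0.751 (stated 75%). One-sided Φ(0.993) = 0.840 (stated 85%).
- Switching: p̄ = (60 + 120)/700 = 0.257, SE0 = 0.0334, SE1 = 0.0325. Two-sided Φ(1.063) = 0.856 (stated 86%). One-sided Φ(1.386) = 0.917 (stated 92%).

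The stated figures are therefore power for 700 women analysed. A continuity-corrected version gives 0.726 and 0.835 two-sided, so it was not the method used.

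**Step 2: look for an allowance elsewhere.** 940 × 0.75 = 705. The 25% is used up before enrolment and leaves nothing for later loss.

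**Step 3: power if 700 are enrolled and some are lost equally across arms**

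| Loss | Analysed | Use, two-sided | Switching, two-sided | Use, one-sided | Switching, one-sided |
|---|---|---|---|---|---|
| 0% | 700 | 75.1% | 85.6% | 84.0% | 91.7% |
| 6.5% (observed) | 654 (280 v 374) | 72.2% | 83.2% | 81.7% | 90.1% |
| 10% (assumed) | 630 (270 v 360) | 70.6% | 81.7% | 80.4% | 89.0% |

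To keep 700 at endline, the baseline target would have had to be 700/(1 − 0.065) ≈ 749 at 6.5% loss, or 700/0.90 ≈ 778 at 10%.

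**Step 4: the trial as run.** Completers by arm are not reported. Splitting 731 in proportion to the randomized arms, the invitation comparison is 731 × 333/784 ≈ 310 v 731 × 451/784 ≈ 420. Power is 76.8% and 87.0% two-sided, and 85.3% and 92.6% one-sided. The targeted-counseling comparison (about 309 v 422) gives the same values to within 0.1 point.

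**The case against.** The strongest reply is that no harm followed. The stopping rule was a floor of at least 700, 782 women were randomized, and the 731 completers exceed the 700 behind Tables 4 to 7. The Analysis Plan also makes the main tests one-sided, and one-sided power stays at or above 80% for both outcomes even if only 700 had enrolled and 10% were lost. All of this stands, and it keeps the point minor.

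A reader might go further and infer that no power figure in the article matches either the plan or the data. The documents do not support that. For 731 completers, one-sided power is about 85% and 93% against the stated 85% and 92%, and the two-sided values are slightly above those stated. The printed figures are also correct, to within about a point, for 700 women analysed. Nor can one conclude that the trial was underpowered against its own statement.

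A second reply is that intention to switch may be measured straight after counseling. Table 3 lists contraceptive preferences and attitudes at that wave, and the article does not say which wave supplies the switching outcome used for power. If it is the counseling session, the 1-month loss rate does not apply to it, so the fall from 86% to 83% is conditional.

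What these replies leave untouched is the label. The surplus over 700 is nowhere presented as an attrition allowance, and stopping at 700 would have given less than the stated power at any non-zero loss.

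**Conclusion.** The point holds as an error in the planning text. The same 700 is the enrolment target and the endline sample, no loss is planned, and the stated power applies to 700 enrolled only with zero attrition. At the trial's own loss rate the overstatement is about 3 points two-sided for both outcomes (75% to 72%, 86% to 83%). One-sided, the values after loss are 82% and 90% against the stated 85% and 92%; about one point of the first gap is there before any loss, since 300 v 400 gives 84%.

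These figures assume equal loss across arms and, for switching, that the outcome is taken at the 1-month follow-up. The practical consequence is small: over-enrolment more than offset the loss, and no decision on design or analysis changes.

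**What to change.** In all four power sections, drop the attrition-adjusted and endline labels and call 700 the baseline target, or else state a planned loss rate. Then give power after loss for 700 enrolled: at 6.5%, 72% and 83% two-sided and 82% and 90% one-sided; at an assumed 10%, 71% and 82% two-sided and 80% and 89% one-sided. State which survey wave supplies the switching outcome and, if it is the counseling session, that the follow-up loss does not apply to it.

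One added sentence could note that 782 were randomized and 731 completed, and that this surplus, rather than a planned allowance, covered the loss. Power for the 731 can be shown as context if the equal-loss assumption is declared.

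The cost is a few lines of text and restated figures, with no additional women and no change to the analysis.
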